### Interventions

During the initial visit, the OH physician will inform the employee about the study and its aims. If the employee agrees to participate, informed consent will be signed. It includes a permission to contact the supervisor, preferably during the same visit, in order to verify whether the work-related arrangements for part-time sick leave are feasible, in case the employee is allocated to the intervention group. If the supervisor disagrees, the employee will be excluded from the trial.

Once the agreements from the employee and the supervisor have been obtained and before the randomisation has occurred, the physician will determine the length of the sickness absence based on symptoms (Table 2), clinical findings [12,13] and background information (Table 3). If the employee is allocated to part-time sick leave (intervention group), daily work load will be reduced by restricting work time. Also, if necessary, remaining work tasks will be modified so that working should be possible despite the symptoms. In the control group, work load will be eliminated with full-time sick leave. Both groups will receive appropriate medical advice, and the need for medical treatments and a control visit will be determined as usual.

**Table 2 T2:** Health-related variables inquired at baseline and during follow-up

**Outcome**	**Measure**
Main reason for the visit (at baseline)	Localisation and characteristics of pain
Pain intensity	Scale from 0 to 10
Interference with work activities	Scale from 0 to 10
Interference with sleeping	Scale from 0 to 10
Self-assessed functioning	Oswestry Back questionnaire [15] Quick DASH (Disabilities of the Arm, Shoulder and Hand) [16] COAT (Comprehensive Osteoarthritis Test) for lower extremities [17]
Productivity at work	Quantity and Quality of work [26]
Adjustments at work (during follow-up)	Description of change in physical work load (structured and open questions)

**Table 3 T3:** Explanatory variables measured at baseline

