### Outcomes

The main outcomes are the number of days from the initial visit to the return to regular work activities and the total number of part- and full-time sick leave days during one- and two-year follow-up. Other outcomes are changes in symptoms as well as in self-assessed functioning during follow-up [15-17].

Data on self-assessed workload will be collected after the initial visit and during part-time sick leave in order to recognise physically strenuous work tasks relevant to MSDs [18,19], as well as to list the work adjustments made during the part-time sick leave. This will be included in an internet based questionnaire together with the symptoms and background variables [20-25]. The questionnaire will be sent to the employees immediately after recruitment and at one, three, eight, 12 and 52 weeks. Those without access to internet will be telephone-interviewed by a researcher. Also, the supervisors in both groups will be interviewed by phone after the employee has returned to work.

Participating employees, their supervisors, OH personnel, human resources management, as well as occupational safety and trade union representatives will be interviewed, and the feasibility of early part-time sick leave will be evaluated based on the qualitative information collected in the interviews. From those employees, who decline to participate, only information on age and gender will be collected. They will also be offered a possibility to provide the main reason for not participating. This can be done with an anonymous questionnaire that can be returned in a closed envelope directly to the researchers. The reason for a negative response from the supervisor is also documented.

The follow-up is extended to two years with the purpose of detecting the possible longer-lasting effects on e.g. illness behaviour. One and two years after the initial visit, the dates and diagnoses of all sickness absences (including those prescribed outside OH services) will be collected from the OH units.

Patient enrolment started in January 2008 and it is planned to last until July 2009. Follow-up of the last participants will finish two years later in 2011. Based on the pilot study, however, preliminary results on the feasibility of early part-time sick leave will be available already in 2008.

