### Statistical methods

A survival analysis will be used to study the time to return to work in the intervention and control group. The amount of sick leave days will be analysed at 12 and 24 months, and the associations between the outcomes and background variables will be analysed using general linear models. In addition, the change in symptoms and disability indices will be studied at various time points using general linear models for repeated measurements.

Subgroup analyses will be performed in relation to patient compliance, type of work, adequacy of work adjustments, previous sick leaves, pain characteristics (such as localisation, duration), and level of disability at baseline. All analyses will be made based on an intention-to-treat principle.

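### Two planned subgroup factors, patient compliance and adequacy of work adjustments, arise after open allocation, so between-arm comparisons within their levels lose the protection of randomisation that the intention-to-treat statement implies

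*Protocol article*

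**What the plan says.** The subgroup plan is in the protocol article, Statistical methods: "Subgroup analyses will be performed in relation to patient compliance, type of work, adequacy of work adjustments, previous sick leaves", followed by "pain characteristics (such as localisation, duration), and level of disability at baseline". The baseline qualifier at the end attaches to level of disability, not to compliance or adequacy of adjustments. The sentence immediately after it reads: "All analyses will be made based on an intention-to-treat principle". Neither factor is marked as exploratory, per-protocol or non-randomised.

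On timing, Table 2 (Interventions section) has a row for "Adjustments at work (during follow-up"), and the Outcomes section plans "to list the work adjustments made during the part-time sick leave". Before randomisation the supervisor is contacted "to verify whether the work-related arrangements for part-time sick leave are feasible, in case the employee is allocated to the intervention group", and the physician sets the length of absence. For the comparator, the Interventions section says: "In the control group, work load will be eliminated with full-time sick leave".

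**The concern.** A subgroup comparison of randomised arms is protected only if the subgroup is defined by something allocation cannot have changed. Type of work and previous sick leave meet that condition. How well an employee kept to the assigned leave, and how adequate the adjustments turned out to be, do not. Both come after an unblinded allocation. According to the Discussion, the intervention itself depends on decisions by the employee, supervisor, colleagues and employer. Within a level of such a factor, the part-time and full-time employees being compared have been selected differently.

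The Background attributes the null result of an earlier cluster-randomised study of active sick leave partly to low uptake. If the overall result here were null, a finding restricted to those who complied, or whose work was well adjusted, would be a natural fallback. As written, it would carry an intention-to-treat label that it had not earned.

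**Working it through.** **Step 1. Place each factor before or after randomisation.**

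| Factor | When it is known | Exists alike in both arms? |
|---|---|---|
| Type of work | Before | Yes |
| Previous sick leaves | Before (occupational health database, Table 3) | Yes |
| Pain characteristics, baseline disability | Can be measured before | Yes |
| Patient compliance | Only after allocation; not defined in the article | No: the regimens to comply with differ |
| Adequacy of work adjustments | During follow-up (Table 2), during part-time leave (Outcomes) | No: controls are not at work during the assigned leave |

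What is settled before randomisation is the supervisor's view that arrangements are feasible and the length of absence. Neither is compliance, and neither is the adequacy of the adjustments actually made.

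**Step 2. Can a spurious difference arise with no treatment effect?** The plan has no figure of its own to reproduce. The inputs below are assumptions, apart from the 300 per arm and the 10–15% drop-out in the Sample size section.

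- Return to regular work by a given day: 70% in both arms (no true effect).
- Non-compliant share of the part-time arm: 20%.
- Return among non-compliers: q, varied.
- Comparison: part-time compliers against all controls.

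Return among compliers = (0.70 − 0.20 × q) / 0.80.

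- q = 0.50 (non-compliers recover poorly): (0.70 − 0.10)/0.80 = 0.75, a difference of **+5 points**.
- q = 0.70 (compliance unrelated to recovery): (0.70 − 0.14)/0.80 = 0.70, no difference.
- q = 0.90 (non-compliers recover quickly): (0.70 − 0.18)/0.80 = 0.65, a difference of **−5 points**.

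Five points is half of the 10-point difference for which the trial is sized.

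**Step 3. Effect on a nominal two-sided 5% test.** With 10% drop-out there are 300 × 0.90 = 270 controls and 270 × 0.80 = 216 compliers.

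- q = 0.50: SE = √(0.75 × 0.25/216 + 0.70 × 0.30/270) = 0.041; z = 0.05/0.0406 = 1.23; rejection probability about 23%.
- q = 0.90: SE = √(0.65 × 0.35/216 + 0.70 × 0.30/270) = 0.043; z = −0.05/0.0428 = −1.17; rejection probability about 22%.

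With 15% drop-out (204 against 255) the two figures are about 22% and 21%.

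**Step 4. A second illustration, comparing like-labelled groups.** This is a simulation with no treatment effect and 50% return in both arms. A standard normal prognostic factor acts with log-odds 0.8 on return and, in the part-time arm only, on compliance (about 71% compliant). Controls comply 95% of the time regardless of prognosis. Overall return is 50.0% in each arm. Among compliers it is 53.7% against 50.0% (+3.7 points). Among non-compliers it is 41.1% against 49.9% (−8.8 points). Comparing compliers with compliers therefore does not remove the problem. All inputs are again assumed.

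**The case against.** The strongest reply is that the subgroup sentence does not say which groups will be compared. A description within the part-time arm fits the wording, and for adjustments it is arguably the natural reading, since the Outcomes section lists those made during part-time leave. This stands in part: the comparison with all controls in Steps 2 and 3 is supplied here, not stated. But the two factors share one list with baseline factors for which a between-arm comparison is clearly meant, and nothing sets them apart.

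A reader might infer that the plan would produce a favourable result for those who comply. The document does not support that. Compliance is undefined. Moving from part-time to full-time leave after re-evaluation is a route the protocol permits, so it cannot simply be counted as non-compliance. The Discussion also describes employees choosing to return earlier than recommended. If they count as non-compliers, the compliers are the slower recoverers and the bias runs against part-time leave. Even under the illustrative 5-point bias, the test would usually not reject.

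A reader might also call this a flat contradiction of intention-to-treat. Employees can be kept in their allocated arm within each level, so the label can be met literally. What is lost is the comparability that the principle exists to protect.

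Finally, Table 2 does not restrict adjustments to one arm, and supervisors in both groups are interviewed after return to work. Controls might therefore have adjustments recorded later. That is a different exposure at a different time, so it does not supply a like-for-like group.

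**Conclusion.** The point holds in a limited form. Two of the listed subgroup factors are observed only after open allocation and can depend on arm and prognosis, and one of them has no like-for-like counterpart among controls during the assigned leave. Between-arm comparisons within their levels could show an effect in either direction when there is none, and a blanket intention-to-treat statement should not cover them. This is a stated analysis choice, not a detail left to an unseen analysis plan.

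Neither size nor direction can be derived from the document; the ±5 points and the roughly one-in-five rejection rates depend on the assumed 70%, 20% and q, and on compliers being compared with all controls. It would be wrong to infer that the trial's main conclusions are at risk: the analyses of time to return to regular work and of sick leave days by allocated arm are untouched. It should be fixed, but it is not critical.

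**What to change.** In Statistical methods:

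- Restrict treatment-by-subgroup analyses, tested by interaction terms, to factors fixed before randomisation: type of work, previous sick leaves, pain characteristics, and disability measured before allocation. The first questionnaire goes out just after recruitment, so state which measurement serves as baseline.
- Take patient compliance and adequacy of work adjustments off that list and out of the scope of the intention-to-treat sentence.
- Report adequacy of adjustments descriptively, within the part-time arm only.
- Define compliance, and label any analysis by it as exploratory and non-randomised.
- A complier-average causal effect, with randomisation as instrument, is optional. If used, state its exclusion restriction. That assumption is doubtful for employees who tried part-time work and then switched, because allocation exposed them to the intervention even if they are classed as non-compliant.

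The cost is a wording change and weaker claims from two secondary analyses. No new data are needed.

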### Ethics

The Coordinating Ethics Committee of Hospital District of Helsinki and Uusimaa has granted approval for this study.

### Clinical Trial Register

This study has been registered at International Standard Randomised Controlled Trial Number Register, register number ISRCTN30911719

## Discussion

The target of this intervention is to adjust work (both work time and demands) to accommodate the disabled employee so that he or she can continue working during recovery from a MSD. As pointed out by Durand et al [27], in this type of intervention work becomes an object of the intervention itself raising various methodological challenges. In addition to the medical judgement by the physician, the intervention requires actions and decisions made by the employee, supervisor, colleagues and employer – each with their own values, objectives, interests, and training [28].

Sickness absence is usually considered as a consequence of a health disorder rather than its treatment and, therefore, in most studies, it has been used as an outcome measure. In this trial, however, the mode of sick leave (part- or full-time) is used as an intervention to affect the outcome, i.e., the quantity of sick leave (number of sick leave days). The potential benefit of the intervention, i.e., the difference in the total number of full- or part-time sick leave days between the intervention and control group, will arise either from the employee's decision to return to regular work earlier than recommended by the physician, or from the need for additional part- or full-time sick leave during the follow-up period.

It is essential in this intervention that the physician determines the length of the disability before allocation, and adheres to this when prescribing either part- or full-time sick leave. This is to avoid bias that might occur if the length of the sick leave is determined differently for part- and full-time sick leave. The risk for bias concerns also the possible control visit, during which the allocation to further part- or full-time sick leave is again open to both the physician and the employee. Inappropriately timed return to regular work in either group should, however, show in secondary outcomes, such as pain, functional status, employee satisfaction and costs.

Despite the extensive amount of quantitative data collected in this trial on individual, ergonomic, psychosocial and economic factors, we do not have the means to quantify all the aspects of the arrangements made at the workplaces during part-time sick leave. Acknowledging the potential effect of this contextual process on the outcome of the intervention, we aim to collect all relevant qualitative data during the study from the employee and the supervisor.

This is the first randomized controlled trial to our knowledge to investigate the effectiveness of early part-time sick leave in comparison to conventional full-time sick leave in musculoskeletal symptoms. The results and the increased knowledge will assist in better decision making process regarding the management of disability related to MSDs.
